### 3.5. Recommended In- and Exclusion Criteria

Participants are eligible if they:have an identified start of pregnancy date.are enrolled in the healthcare system for a least 12 months prior to Time zero (date of vaccination).have at least one day of follow-up after Time zero for maternal outcomes and at least 10 months of follow-up after the LMP for birth and pregnancy outcomes.

Participants are excluded if they:are exposed to an RSV vaccine prior to the current pregnancy or before or after the gestational week for which the vaccine is licensed (vaccination in a prior pregnancy is permitted).cannot be linked in the data source to their child (mother-child linkage).

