## 3. Methods

### 3.1. Study Design

We recommend an observational retrospective comparative cohort study of pregnant women who receive the RSV vaccine compared to an unexposed pregnant comparator group (or an active comparator group when there is one). To assess whether the RSV vaccine increases the risk of any adverse outcome in pregnancy or offspring, we propose designing the study to emulate a hypothetical pragmatic randomised trial (Table 1) [16]. This trial would assess the safety of administering one dose of the RSV vaccine between 24 and 36 weeks of gestation in pregnant women compared to pregnant women who do not receive an RSV vaccine (Figure 1A). As we cannot truly randomise participants, we need to emulate this feature by carefully addressing confounding biases through various techniques such as matching and careful assessment of inclusion criteria. These techniques also have the potential to address both selection bias and immortal time bias. Time zero, designated as day 0, marks the point at which the eligibility criteria are fulfilled, and the RSV vaccine is administered to the pregnant woman.

At Time zero, exposed participants should be matched to unexposed pregnant participants eligible to receive the vaccine (1:N ratio) based on (Figure 1B):Gestational age (same week of gestation) to account for timing of vaccination in pregnancy and the risk of preterm birthCalendar time (same week) because of RSV seasonality and probability of exposureMaternal age (year of birth) because of the association with adverse pregnancy outcomesImmunocompromised status because of the association with adverse maternal outcomesHigh-risk pregnancy because of the association with adverse pregnancy outcomes

Additional characteristics may be added that would confound the association.

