A primary analytical concern is the gestational age at Time zero, which directly impacts the risk of preterm birth. Therefore, it is imperative to ensure a robust match on gestational age, and in fact, we recommend emulating a series of separate target trials for different gestational ages at vaccination, i.e., 24, 25, 26, …, or 36 weeks to study effect modification [17]. Follow-up of the exposed and unexposed (or active comparator) pregnant women should start on day 1, and end at the earliest of N months after birth depending on the outcome being measured, maternal death, disenrollment or migration, end of data availability in the data source, treatment crossover, or occurrence of a given outcome. Treatment crossover, or protocol violation, occurs when previously unexposed pregnant women in the matched comparator cohort receive vaccination with an RSV vaccine during pregnancy. To uphold statistical power, unexposed pregnant women within the matched comparator cohort ought to be censored upon treatment violation, while exposed pregnant women should remain uncensored (see Section 3.10). When unvaccinated pregnant women receive an RSV vaccine, they become eligible for inclusion in the vaccinated cohort (Figure 1C). Follow-up of offspring to assess birth outcomes will depend on the risk window for measuring the outcome and will end at the earliest of N months of age, neonatal death, disenrollment or migration, end of data availability in the data source, or occurrence of a given outcome.

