### 3.4. Study Population

The study population comprises all pregnant women who receive an RSV vaccine during pregnancy from the earliest indicated timing of gestation for which the vaccine is licensed and a matched comparator group of pregnant women who did not receive the RSV vaccine or received another RSV vaccine. Identification of pregnancies may vary across data sources which is very important since most data sources that link to birth registries only detect pregnancies when they end. Validated data source-specific algorithms or the ConcePTION pregnancy algorithm could be employed to determine the start and end dates of ongoing pregnancies. The ConcePTION algorithm was created to identify ongoing pregnancies using diagnosis and procedure data related to pregnancy [20]. The identification of ongoing pregnancies is important to avoid selection bias towards pregnancies that end prematurely. In instances where pregnancy data are only available when the pregnancy has ended, a minimum of 10 months of administrative follow-up from the last menstrual period (LMP) in the data source, unless they died, is recommended for all pregnancy and birth outcomes. This period covers the gestational period plus an additional month to identify offspring outcomes at birth [17]. It is important to anticipate that women may have more than one pregnancy, and those subsequent pregnancies could be included to increase power.

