In addition to outcome misclassification, it is also crucial to address exposure misclassification. Since RSV vaccination has only recently received approval for maternal immunisation, and many countries’ National Immunisation Technical Advisory Groups have yet to decide on its inclusion in routine immunisation schedules, it can be challenging to determine whether current data sources accurately capture RSV vaccination. This challenge is reflected by the current situation in Europe, where other maternal immunisation practices vary widely across countries, and some prefer to provide monoclonal antibodies or vaccines to neonates [2,48] Therefore, before commencing data collection, it is imperative to liaise with relevant public health organisations to understand if and how RSV vaccination will be integrated into routine immunisation programs for maternal immunisation and in which settings it is provided. Subsequently, it is essential to verify if the data source adequately captures this information and compare it with national statistics to ensure comprehensive coverage and prevent exposure misclassification in the comparator group.

It is important to note that a non-exposed comparator group may be chosen because presently there is only one approved maternal vaccine for preventing RSV infection in offspring. In the event that other RSV vaccines receive approval, it is crucial to consider their inclusion in the study design. This necessitates either incorporating all different RSV vaccines in the exposed group or excluding women specifically vaccinated with other RSV vaccines from the unexposed group.

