Follow-up period	For each maternal participant, including her fetus, data on adverse events were collected from the time of informed consent to 1 month after injection, and data on serious adverse events were collected from the time of informed consent through 6 months after delivery. Safety end points in the infant participants included adverse events from birth to 1 month of age. Additional safety end points were serious adverse events and newly diagnosed chronic medical conditions from birth through 12 to 24 months of age. For vaccine efficacy outcomes in infants started at 72 h after birth and continued through 12 to 24 months of age.	Follow-up of the exposed and unexposed (or active comparator) pregnant women should start on the day after eligibility criteria are fulfilled and end at the earliest of N months after birth depending on the outcome being measured, maternal death, disenrollment or migration, end of data availability in the data source, treatment crossover, or occurrence of a given outcome. Follow-up of offspring to assess birth outcomes will depend on the risk window for measuring the outcome and will end at the earliest of N months of age, neonatal death, disenrollment or migration, end of data availability in the data source, or occurrence of a given outcome.
Outcome	Safety: The primary safety end points were reactogenicity and adverse events in the maternal participants and adverse events and newly diagnosed chronic medical conditions in the infants. Efficacy: The two primary efficacy end points were medically attended severe RSV-associated lower respiratory tract illness and medically attended RSV-associated lower respiratory tract illness.	For post-authorisation safety study purposes, the focus is solely on safety, encompassing preterm birth, stillbirth, hypertensive disorders of pregnancy, low birth weight (LBW), small for gestational age (SGA), and Guillain-Barré Syndrome (GBS).
Causal Contrasts of Interest	Per protocol analysis	Observational analog of per-protocol effect
Analysis	Per protocol analysis	Same per-protocol analysis, except for restriction to pregnancies without loss-to-follow up

**Table 2 vaccines-13-00272-t002:** Outcomes of interest.

Outcomes	Clinical Definition	Pregnancies Among Which the Outcome Will be Ascertained	Exposure Risk Window for Outcome

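### Section 3.5, read literally, excludes comparators for RSV vaccination after time zero; this removes only term pregnancies from the comparator and conflicts with the censoring rule, and the follow-up rules need the same reconciliation

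*Protocol article*

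**What the plan says.** **Eligibility and time zero.** Section 3.1 states: "Time zero, designated as day 0, marks the point at which the eligibility criteria are fulfilled, and the RSV vaccine is administered". It adds of matching and careful eligibility assessment: "These techniques also have the potential to address both selection bias and immortal time bias".

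**Exclusion.** Section 3.5 excludes participants, with no distinction between cohorts, who are "exposed to an RSV vaccine prior to the current pregnancy or before or after the gestational week for which the vaccine is licensed".

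**Later-vaccinated comparators.** Section 3.1 defines crossover as a comparator receiving an RSV vaccine during the pregnancy, with no gestational limit, and says that "unexposed pregnant women within the matched comparator cohort ought to be censored upon treatment violation". Section 3.10.2 repeats this and calls for inverse probability of censoring weights for crossover.

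**Follow-up.** Section 3.4 says that, where a source shows pregnancies only once they have ended, "a minimum of 10 months of administrative follow-up from the last menstrual period (LMP) in the data source, unless they died, is recommended". Section 3.5 makes it a general eligibility condition: "at least 10 months of follow-up after the LMP for birth and pregnancy outcomes". The Analysis row of Table 1 gives the emulation as "Same per-protocol analysis, except for restriction to pregnancies without loss-to-follow up". Section 3.1 and the follow-up row of Table 1 instead list death, disenrolment or migration, end of data and crossover as events that end follow-up.

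**The concern.** Take a comparator matched at week 30 and vaccinated at week 37. Section 3.5 removes her from the study; section 3.1 keeps her and censors her at vaccination. Both cannot be followed.

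The choice matters because the exclusion is not neutral. She had to be still pregnant after the preterm risk window closed in order to be vaccinated then, so her removal is conditional on her not having had the outcome. No matching removal occurs among exposed women, whose qualifying dose is already known at their own time zero. The comparator's preterm risk therefore rises and the risk ratio falls. Section 4 names preterm birth as the primary outcome because of safety concerns, so this is the unhelpful direction. Time from vaccination to birth is affected in the same sense, because the removed comparators have long gestations.

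The two follow-up rules raise a different question: whether women are selected on completing follow-up when the plan elsewhere says to censor them.

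**Working it through.** **1. The plan's own figure.** Section 3.9 cites about 1200 pregnancies to detect a risk ratio of 1.5 for preterm birth, with alpha 5% and 80% power; 6.0% is the top of its prevalence range. For 9% versus 6%, two-sided, 1:1, without continuity correction:

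n = [1.96·√(2 × 0.075 × 0.925) + 0.842·√(0.09 × 0.91 + 0.06 × 0.94)]² / 0.03² ≈ 1209 exposed women.

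This agrees with about 1200 if that means exposed women at 1:1, and it supports 6% as the baseline risk. The point itself does not depend on this figure.

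**2. Excluding comparators vaccinated after 36 weeks 6 days.** Inputs: comparator preterm risk p = 0.06; preterm risk window closing at 36 weeks 6 days (Table 2); f = share of term comparators so vaccinated (assumed, as the protocol gives none). Only term pregnancies leave, so

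comparator risk = p / [p + (1 − p)(1 − f)], and observed RR = true RR × [1 − 0.94f].

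| f (assumed) | Comparator risk | Observed RR, true 1.0 | Observed RR, true 1.5 |
|---|---|---|---|
| 1% | 0.06/0.9906 = 6.06% | 0.99 | 1.49 |
| 3% | 0.06/0.9718 = 6.17% | 0.97 | 1.46 |
| 5% | 0.06/0.9530 = 6.30% | 0.95 | 1.43 |

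With 1200 per arm and a true ratio of 1.5, power falls from 79.7% to 78.0% at f = 1% and 70.3% at f = 5%.

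**3. Censoring instead.** Simulations with no vaccine effect (1,000,000 pregnancies each, 6% preterm, matching at week 24, 28 or 32, assumed weekly vaccination rates of 2%, 5% or 10% up to week 37, unrelated to birth timing) were analysed by Kaplan-Meier with censoring at vaccination. The risk ratio was 0.994 to 1.005, so the section 3.1 rule is unbiased for crossover within the window when vaccination is unrelated to risk. The weights in section 3.10.2 are for the case where it is related.

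**4. Restricting to pregnancies without loss.** If shares a of preterm and b of term pregnancies are lost, the observed risk is p(1 − a) / [p(1 − a) + (1 − p)(1 − b)]. The loss rates are assumed.

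- 20% of preterm and 5% of term lost in both arms: comparator 0.048/0.941 = 5.10%, exposed 0.072/0.9365 = 7.69%. A true 1.5 becomes 1.507; a true 1.0 stays 1.0.
- 20% of exposed preterm lost, 5% in every other cell: a true 1.5 becomes 7.69/6.00 = 1.28; a true 1.0 becomes 5.10/6.00 = 0.85.

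Outcome-dependent loss alone does almost nothing. Loss that depends on exposure and outcome together does.

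**5. The 10-month rule side by side.** Section 3.4 makes it administrative, excepts death, and limits it to sources that see only completed pregnancies. Section 3.5 has none of these qualifiers. Read literally, a woman who dies or disenrols early is ineligible under section 3.5 but followed and censored under section 3.1.

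**The case against.** The best defence is that section 3.1 already gives the specific rule for comparators, at any gestation, and that the section 3.5 exclusion is meant for vaccinated candidates, for whom an off-window dose is known at their own time zero. For them it is a proper baseline criterion. That stands. It does not cure the wording, which names participants in general and includes vaccination after the licensed weeks.

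Three stronger readings are tempting and not supported:

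- **That every later-vaccinated comparator is dropped.** The exclusion reaches only vaccination outside the licensed weeks. Crossover inside the window, likely the larger part, is censored under section 3.1.
- **That section 4 adds a large bias by** "excluding women specifically vaccinated with other RSV vaccines from the unexposed group". The remark is conditional on other products being approved, is one of two options, and does not say that it reaches vaccination after time zero. No size can be attached to it.
- **That the follow-up rules are also immortal time.** An administrative 10-month rule, as in section 3.4, does not depend on what happens to the woman and guards against selecting pregnancies that end early. The loss restriction sits in the Analysis row of Table 1, not among the eligibility criteria, and is openly listed as a departure from the target trial. Its conflict is with censoring at disenrolment in section 3.1 and in Table 1's own follow-up row; section 3.10.2 mentions weights for crossover only.

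It is also fair that this is a template with recommended criteria, to be adapted locally. But a template's inconsistent wording is liable to be copied.

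**Conclusion.** The point holds in a limited form. Sections 3.5 and 3.1 give incompatible instructions for comparators vaccinated after the licensed weeks. The literal section 3.5 rule selects on the future and lowers the preterm risk ratio. The direction is certain; the size is not. At 6% baseline risk the ratio falls by about 0.94% for each percentage point of term comparators removed, so it is small unless vaccination after the licensed weeks is common.

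The 10-month rule and the loss restriction are separate inconsistencies. The first is met by restoring the section 3.4 wording. The second is a possible selection bias of unknown size, material only if loss depends on both exposure and outcome. All vaccination and loss rates used here are assumptions.

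**What to change.** - **Section 3.5, general:** state that the criteria are assessed with information up to time zero.
- **Section 3.5, off-window vaccination:** apply the exclusion only to vaccination at or before time zero. Treat any later RSV vaccination of a comparator as crossover under section 3.1, with censoring and weights. For preterm birth, a comparator vaccinated after 36 weeks 6 days has completed the risk window and should count as a known non-event.
- **Section 3.5, 10-month rule:** word it as administrative, so that the last menstrual period plus 10 months falls before the data-source end date, and restore the death exception.
- **Table 1, Analysis row:** replace the restriction with censoring at loss to follow-up and inverse probability of censoring weights.
- **Section 4:** if other RSV products are approved, apply that exclusion only to vaccination before time zero.

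The cost is rewording in three places, slightly more censored records and some extra weight modelling. No new data are needed.

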### 3.2. Study Setting

To have sufficient power, we recommend using real-world secondary data derived from electronic health records or administrative claims data that can be linked on an individual level to birth registries and outcomes in offspring (mother-child linkage). The specific study setting will be defined by the availability and nature of the data source(s) utilised and will depend on the country or region covered by the data source. To assess whether data sources are fit for purpose, we stress the importance of ascertainment the accuracy of estimating the start and end of pregnancy, the ability to detect ongoing pregnancies, the capacity to identify exposure to RSV vaccines including timing of vaccine dose, the feasibility of linking mother and child, the capability to measure outcomes and confounders of interest, and the lag time for data availability for each study component. We recommend the use of quality indicators and external benchmarks to assess whether a data source is fit for purpose [18,19]. Key aspects of this evaluation include:Population coverage: The data must cover a representative sample of the population under study. This includes demographics such as age, sex, ethnicity, and geographic location.Data granularity: The data must be granular enough to capture individual-level information on healthcare encounters, including diagnoses, procedures, prescriptions, and outcomes.Longitudinal data: Longitudinal data, tracking individuals over time, is essential for understanding disease progression, treatment patterns, and outcomes.Data quality: High-quality data is crucial for reliable analysis. This involves accurate information recording, standardised coding systems, and measures to address missing or erroneous data.Data linkage: The ability to link data across different sources (e.g., primary care, hospitals, pharmacies, birth registers) enables a comprehensive view of healthcare utilisation and outcomes.Privacy and ethical considerations: Data sources must adhere to strict privacy regulations and ethical guidelines to protect patient confidentiality and ensure informed consent.Timeliness: Timely updates ensure that researchers can access the most current information, allowing for real-time or near-real-time analyses.

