#### 3.10.2. Measures of Effect

Primary analyses should estimate counts, proportions, and risk or rate ratios with 95% CI for events occurring and measurable during pregnancy, and counts, proportions, and prevalence ratios with 95% CI for outcomes measurable at birth. Comparison of outcomes by exposure status should be conducted using multivariable generalised linear models. These analyses should control for potential confounding by matching. Balance of covariates should be analysed using standardised mean differences (SMDs), some characteristics and risk factors for the exposure or outcomes may remain unbalanced, which should be analysed using plots of SMDs. To address this, propensity score methods can be employed and propensity scores can be adjusted or additionally matched on if necessary [40]. To obtain more power for the analysis of preterm birth, we recommend that time from vaccination to birth should be analysed separately [21,22].

The primary analyses may face-selective censoring due to treatment crossover in the comparator cohort, necessitating the use of inverse probability censoring weights. To maintain statistical power, unexposed pregnant women in the matched comparator cohort should be censored upon treatment violation, while exposed pregnant women should not be censored. Weights can be used to correct for the bias introduced by such censoring, ensuring more accurate and reliable results. Additionally, a sensitivity analysis can be conducted to explore the effect of censoring the matched pair if treatment crossover happens in the previously unexposed pregnant woman. Another sensitivity analysis may be carried out to explore the effect of exclusion of medically indicated iatrogenic births.

For subgroup analyses, secondary analyses can be conducted among immunocompromised or high-risk pregnancies and stratified by weeks of gestation at the time of vaccination.

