**Pregnancy outcomes**			
Preterm birth [23]	Preterm birth is defined by the WHO as babies born alive before 37 weeks of pregnancy are completed. It is further subcategorised based on gestational age: Extremely preterm (less than 28 weeks) Very preterm (28 to less than 32 weeks) Moderate to late preterm (32 to 37 weeks)	Pregnancies ending with live births	From time of vaccination to before week 37 of gestation (36 weeks and 6/7 days)
Time between vaccination and birth	Time between vaccination and birth in days.	Pregnancies ending with live and non-live births	From time of vaccination to time of birth
Stillbirth [24]	Stillbirth is defined by the WHO as the death of a foetus that has reached a birth weight of 500 g, or if birth weight is unavailable, gestational age of 22 weeks or crown-to-heel length of 25 cm. It is further subcategorised based on gestational age: Late foetal deaths (greater than 1000 g or after 28 weeks) Early foetal deaths (500–1000 g or 22–28 weeks)	Pregnancies ending with live and non-live births	From time of vaccination to end of pregnancy

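### The blanket mother-child linkage exclusion in Section 3.5 contradicts Table 2's live and non-live birth populations and can leave stillbirth under-counted or inestimable

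*Protocol article*

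**What the plan says.** The exclusion list in Section 3.5 removes participants who "cannot be linked in the data source to their child (mother-child linkage". It is not limited by outcome or to live births. The follow-up criterion in the same section is split by outcome: women must "have at least one day of follow-up after Time zero for maternal outcomes and at least 10 months of follow-up after the LMP", the ten-month part applying to birth and pregnancy outcomes.

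Table 2 sets the population outcome by outcome. Stillbirth, time between vaccination and birth, hypertensive disorders and GBS use "Pregnancies ending with live and non-live births". Preterm birth, low birth weight (LBW) and small for gestational age (SGA) use "Pregnancies ending with live births". Stillbirth is the "death of a foetus that has reached a birth weight of 500 g", with gestational age or length as fallbacks.

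Section 3.2 asks for data that can be "linked on an individual level to birth registries and outcomes in offspring (mother-child linkage", without saying whether stillborn offspring have such a link. Section 3.10.2 asks for "counts, proportions, and risk or rate ratios with 95% CI for events occurring and measurable during pregnancy", so absolute and relative measures are both reported. The analysis row of Table 1 reads "Same per-protocol analysis, except for restriction to pregnancies without loss-to-follow up" and does not mention linkage.

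**The concern.** Applied literally, the exclusion overrides four of the seven population definitions in Table 2. In a source that gives only live-born children a record to link, it deletes the stillbirths that the study is meant to count. It also drops women whose hypertensive disorder or GBS could be read from their own record.

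The timing is a second problem. Section 3.1 places Time zero where eligibility is met, but linkage is known only after birth and may depend on how the pregnancy ended. Eligibility is then conditioned on a later event related to the outcome, which a target trial emulation should avoid.

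At stake is a key safety outcome: a low or empty stillbirth count could be read as reassurance when the eligibility rule produced it. The article is a template for reuse, so the rule would be carried into other studies.

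**Working it through.** **The passages side by side**

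- Linkage rule (3.5) against Table 2: one population for all outcomes against outcome-specific populations that include non-live births. They agree only if every non-live birth is linkable, which is not stated.
- Linkage rule against the one-day follow-up rule (3.5): a woman who leaves the data before delivery satisfies the latter for maternal outcomes but has no child to link. The GBS window is 42 days, so after vaccination at 24 weeks it closes at 24 + 6 = 30 weeks, well before a term birth.
- Linkage rule against Section 3.4: that section wants ongoing pregnancies identified, to avoid selecting those that end early. An ongoing pregnancy has no child to link.
- The censoring weights in 3.10.2 deal with treatment crossover, not linkage failure.

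**The plan's own figure**

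Section 3.9 gives about 1200 pregnancies for RR 1.5 in preterm birth. With 6% against 9% (6% is the top of its prevalence range), two-sided alpha 5%, 80% power and 1:1:

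n = [1.96·√(2·p̄·(1−p̄)) + 0.8416·√(p1(1−p1) + p0(1−p0))]² / (p1−p0)²

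with p̄ = 0.075 this gives 1209 per group, which reproduces the figure as a per-group count. Preterm birth is restricted to live births, so this number does not depend on losing stillbirths. The same formula is used below.

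**Inputs for stillbirth**

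Alpha 5%, 80% power and RR 1.5, 2.0 and 4.0 come from Section 3.9. Assumed: two-sided testing; 1:1 matching; stillbirth risk 0.2% (the low end of the Section 3.9 range, which the text does not assign to an outcome), with 0.5% as an alternative; and the linkage probabilities s (stillbirths) and l (live births).

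Observed risk = p·s / [p·s + (1−p)·l]

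**Absolute risk and power** (0.2%; power and sample size use l = 1)

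For RR 2.0 with s = 1, n = 11,737 exposed. That group expects 11,737 × 0.4% ≈ 47 stillbirths, against 11,737 × 0.2% ≈ 23 in the comparator.

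| s | Exposed needed, RR 1.5 | Exposed needed, RR 2.0 | Power at the s = 1 sample size |
|---|---|---|---|
| 1 | 39,146 | 11,737 | 80% |
| 0.5 | 78,100 | 23,409 | 51% |
| 0.1 | 389,738 | 116,781 | 14% |
| 0 | no events | no events | RR undefined |

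With l = 0.95, an unexposed risk of 0.2% is observed as 0.105% at s = 0.5 and 0.021% at s = 0.1.

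**RR, equal linkage in both groups** (l = 0.95, risk 0.2% to 0.5%, s from 0.5 to 0.1)

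True 1.5 is observed as 1.501 to 1.503, 2.0 as 2.002 to 2.009, and 4.0 as 4.01 to 4.05. The RR hardly moves, and the small drift is away from 1.

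**RR, linkage differing by exposure** (risk 0.2%, l = 0.95, true RR 1.5)

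- s = 0.4 exposed, 0.5 unexposed: 0.0012/(0.0012 + 0.997×0.95) ÷ 0.0010/(0.0010 + 0.998×0.95) = 1.20.
- s = 0.5 exposed, 0.4 unexposed: 1.88.

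**Hypertensive disorders, all stillbirths dropped** (disorder risk 6%, stillbirth risk 0.5%, stillbirth m times as frequent with the disorder; all assumed)

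The stillbirth risk without the disorder is b = 0.005/(0.94 + 0.06m). For disorder risk h and stillbirth RR r, observed risk = h(1−bmr) / [h(1−bmr) + (1−h)(1−br)], with r = 1 in the unexposed.

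- Vaccine without effect on stillbirth: true 1.5 is observed as 1.500 to 1.501.
- Stillbirth RR 2: true 1.0 is observed as 0.996 (m = 2) or 0.984 (m = 5).
- Stillbirth RR 4, m = 5: true 1.0 is observed as 0.953, and true 1.5 as 1.432.

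**The case against.** The strongest defence is that the criteria are only recommended, that the article asks to be adapted to each setting, and that Section 3.2 makes linkage feasibility and outcome capture part of the fitness-for-purpose check. A birth register that records stillbirths may link them, and then nothing is lost. This stands as a limit: loss of stillbirths is conditional on the source, and the article neither shows that it will happen nor rules it out. It does not reconcile the two texts, because a feasibility check does not tell the adopter which one governs.

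A reader might also infer that the rule makes the vaccine look safe on every outcome that includes non-live births. The documents do not support that. Equal linkage loss leaves the stillbirth RR almost unchanged, and unequal loss can push it up or down. For hypertensive disorders, with linkage failing only through stillbirth and equally in both groups, RR bias needs the vaccine to affect stillbirth and the disorder to be related to it; it stayed under 5% in every scenario run. The same logic applies to GBS, and nothing in the article ties GBS to stillbirth. Time between vaccination and birth would lose its non-live births, but the direction of the effect cannot be derived.

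Finally, Section 3.4 notes that most sources linked to birth registries detect pregnancies only when they end. Unlinked pregnancies may therefore have a less reliable end date or outcome. That is a real cost of relaxing the rule.

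**Conclusion.** The point holds as a contradiction between Section 3.5 and Table 2, and as selection on an event after Time zero. Its practical effect is conditional. Where stillborn offspring have no linkable record, stillbirth proportions fall roughly in line with the share lost, and power falls from 80% to about 51% (half lost) or 14% (90% lost). With no linkage there is no RR to estimate. These sizes rest on an assumed 0.2% stillbirth risk, RR 2.0, 1:1 matching and assumed linkage shares; the text shown gives none of the linkage figures. Material bias in the stillbirth RR arises mainly when linkage differs by exposure, with no fixed direction, and the effect on hypertensive disorder RRs is likely small. A general claim of bias towards safety would go too far. The correction is still warranted, because the rule as written can empty a key safety outcome and no other part of the article corrects for it.

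**What to change.** Remove mother-child linkage from the general exclusions in Section 3.5. Require it only for outcomes that need the child's record: LBW, SGA, and preterm birth where gestational age at birth comes only from that record. Ascertain stillbirth, end of pregnancy, hypertensive disorders and GBS from the maternal record or the birth or foetal-death register. Report the linked percentage by exposure group and pregnancy outcome, so that differential linkage can be seen.

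The text change is short. It has two costs: analysis populations will differ by outcome, as Table 2 already implies, and end-of-pregnancy dates may be less certain in unlinked pregnancies. A sensitivity analysis restricted to linked pregnancies would show how far the second matters.
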